## Reporting Procedures

The DSMB and the Malaria in Pregnancy Safety Working Group will be notified by the principal investigators or their designate within 48 hours about SAE / Grade 4 AEs, while Grade 1-3 AEs will be reported 3 monthly in summary fashion.

### Serious Adverse Event Detection and Reporting

For all events meeting the above described definition of Serious Adverse Events and/or Grade 4 AE, the completion of the Serious Adverse Event report form is required.

The study physicians will inform the PIs immediately of any SAE or Grade 4 AE and complete a Serious Adverse Event Form within the following timelines:

- All deaths, whether associated or not associated, will be recorded on the Serious Adverse Event Form. The Form will be sent by fax to PIs within 24 hours of site awareness of the death.
- Serious adverse events other than death, regardless of relationship, will be reported via fax by the site within 72 hours of becoming aware of the event.

Other supporting documentation of the event will supplied as requested.

The SAE Form will be reviewed by the PIs or their designate, who may request additional information or carry out further investigations. Additionally, an independent local clinician will be appointed to review all SAEs and prepare separate reports for the PIs,DSMB and Malaria in Pregnancy Consortium Safety Working Group

The Principal Investigators will notify the DSMB and Malaria in Pregnancy Consortium Safety Working Group immediately of any serious adverse event, deaths or life-threatening problems that occur in the study within 48 hours and supply all subsequent information at the earliest.

If a grade 4 event is unexplained, or is attributed to study medication, the DSMB chair will instruct the investigators to report the event to the IMR Institutional Review Board, the PNG Medical Research Advisory Committee (MRAC) and the Royal Melbourne Hospital Human Research Ethics Committee (RMH HREC). Reports to the DSMB of severe adverse events (not believed to be due to the study drug) will be submitted to the IRBs electronically on a two-monthly basis.

Reporting of data to the MiP Consortium safety working group will occur in parallel to reporting to the DSMB, e.g. by copy of email report submissions.

Subjects will be withdrawn from the study if they experience a drug related SAE / grade 4 AE.

### Procedures to be followed in the Event of Abnormal Laboratory Test Values or Abnormal Clinical Findings

If a participant is found to have symptomatic severe anaemia (Hb < 6 g/dl with anaemia symptomatology) she will be referred to Modilon Hospital for treatment.

The study coordinator will report such cases as SAE to the PI who will inform the DSMB and MiP SWG.

### Type and Duration of the Follow-up of Subjects after Adverse Events

Management of adverse events will be according to best available practice. The study team will provide referral and transport to Madang (Modilon) Hospital where investigation and treatment will be provided through Government facilities.

All SAEs will be followed until satisfactory resolution or until the Principal Investigator or Study Clinician deems the event to be chronic or the patient to be stable.

## Halting Rules

There are no predefined halting rules, but the DSMB, IMR IRB, PNG MRAC and RMH HREC will each have the power to suspend the study, pending full review of toxicities encountered. The MiP Safety Working Group can make recommendations to the study investigators, DSMB and the IRBs but cannot order stopping or alteration of the study.

# Clinical Monitoring Structure

## Site Monitoring Plan

This study will be monitored both by a specifically constituted Data & Safety Monitoring Board (DSMB) and by an external clinical monitor.

The DSMB will have 3 members a local PNG physician, an Australian physician and a data statistician. The DSMB will generate and hold the allocation code, and will review documentation of all SAE / Grade 4 AEs. Before referral to the DSMB, all SAEs will be reviewed by a locally appointed clinician.

An independent clinician based in Madang will review the CRFs for all SAEs and Grade 4 AEs to ensure their completeness and accuracy, and to make an independent judgement regarding causality. [name] has been appointed to this role

The study will be monitored externally by an external monitor who has experience with monitoring similar studies. S/he will be appointed centrally by the Malaria in Pregnancy Consortium, and s/he will visit the PNG field and laboratory sites every 12 months for the entire duration of the study (anticipated three visits total). S/he will assist the study team with implementation of the study according to ICH GCP standards and will report her/his findings to the principal investigators, the PNGIMR, the Malaria In Pregnancy Consortium Executive Committee, and the DSMB.

# Statistical Considerations

## Study Outcome Measures

The goal of this Protocol is to study assess the efficacy of intermittent preventive treatment with SP&AZ in improving birth outcomes in PNG women. In particular, will determine:

Primary Outcome Measures

- 1. Prevalence of low birth weight (<2500 g) in women receiving SP/AZ and controls

Secondary Outcome Measures

- 1. Prevalence of *P falciparum* at delivery in peripheral, placental and cord blood films and on placental histology, and at second visit by PCR only in peripheral blood films.
  2. Mean maternal hemoglobin concentration at delivery, and proportion of women anaemic (Hb < 11 g/dl).
  3. Prevalence (at enrolment, second treatment, and delivery) and consequences (maternal haemoglobin, birth weight and placental pathology) of *P. vivax* infection in pregnancy
  4. Immune responses to P vivax in pregnant and non-pregnant women
  5. Incidence of symptomatic malaria during pregnancy
  6. Proportion of women carrying azithromycin-sensitive sexually transmitted infections at second treatment visit (28-34 weeks).
  7. Incidence of Adverse Events, including severe adverse events (SAEs), and AEs possibly or probably associated with study medications
  8. Prevalence of drug resistance markers in parasites infecting women in late pregnancy
  9. Prevalence and antibiotic sensitivity patterns of *S. pneumoniae* in nasopharyngeal swabs collected at delivery
  10. Maternal, perinatal and infant mortality rates.
  11. Impact of IPTp on development of immunity to malaria in pregnancy

### Definitions

**Malaria infections: P falciparum and P vivax (Secondary objectives 2 and 4)**

**Microscopy**

Blood smear microscopy is the cornerstone for determining the presence of Plasmodium infections. Blood smears will be evaluated for each type of Plasmodium species and separate counts will be recorded for blood-stage parasitemia of each species and *P. falciparum* gametocytemia. A blood smear will be read as the number of a given Plasmodium spp. parasitized erythrocytes per parallel count of 200 leukocytes. The average leukocyte count for individuals in coastal PNG is 8,000 per µl. Therefore, the parasite count (Plasmodium spp. parasitized RBCs/µl) will be determined by multiplying the number of parasitized RBCs by 40. All blood slides will be read independently by two expert microscopists.

**PCR**

In addition, we will also determine the presence of malaria parasites using PCR-LDR typing (see 6.2.1.2 a). This method has a higher sensitivity than light microscopy and it is therefore common to find infections that are detectable by PCR-LDR, but not by microscopy. Samples will be considered positive for any infections if the mean fluorescent intensity exceed a species specific threshold defined by the mean + 2 SD of negative controls.

Histology

Placental biopsies will be collected at delivery, fixed in 10% neutral buffered formalin,and paraffin embedded. Sections cut onto glass slides will be examined following staining with Giemsa and haematoxylin and eosin. Placentas will be classified as (a) active infection (presence of any parasitised erythrocytes) (b) past infection (presence of malaria pigment haemozoin, in fibrin deposits or in mononuclear leukocytes) and (c) no infection. Active infection will be further divided into active acute (presence of parasites, but not of haemozoin deposits) and active chronic (parasites, and malaria pigment in leukocytes or in fibrin deposits).

Maternal haemoglobin concentration

Measurement of haemoglobin by Hemocue cuvette will be used. Anaemia will be defined as Hb <11.0 g/dl, moderate anaemia as Hb 6.0-8.9 g/dl, and severe anaemia as Hb <6.0 g/dl.

Symptomatic Plasmodium Infection

For diagnostic purposes, a symptomatic Plasmodium infection is defined as any type of Plasmodium parasitemia observed by blood smear and/or a positive rapid diagnostic test, plus an axillary temperature ≥ 37.5° C or a history of febrile illness in last 48 hours.

This definition will be used for analysis of the secondary outcome of symptomatic malaria in pregnancy.

However, for analytical purposes we will use two additional definitions for symptomatic Plasmodium infections: a) any type of Plasmodium parasitemia observed by blood smear and/or PCR/LDR diagnostic assay, plus an axillary temperature ≥ 37.5° C or a history of febrile illness in last 48 hours b) a parasite density of > 1000/μl for *P. falciparum* and/or > 250/μl for non-falciparum, plus an axillary temperature ≥ 37.5° C or a history of febrile illness in last 48 hours.

Asymptomatic Blood-stage Plasmodium Infection

An asymptomatic blood-stage Plasmodium infection is defined as any type of Plasmodium parasitemia observed by blood smear or PCR-LDR confirmation with an axillary temperature less than 37.5° C and no history of febrile illness in last 48 hours.

**Carriage of sexually transmitted infections**

Seropositivity for syphilis will be defined as presence of positive RPR, confirmed by a positive TPHA. Chlamydia trachomatis, Trichomonas vaginalis and N. gonorrhoeae infections will be defined as positive PCR on swabs collected at enrolment and at 28-34 weeks.

### Primary Outcome Measures

1. **Percentage of babies born with low birth weight**

This is the primary objective of the study and will be evaluated by assessing difference in proportion of LBW deliveries between the 2 treatment groups.

When women give birth outside of health facilities, they will be instructed to present with their newborns for checkups as soon as possible, and in any case within 7 days of delivery. Childhood immunisation will be commenced, maternal health assessed, and infant weight measured. Weight within 7 days of birth can be approximated to birth weight.

Only women who receive at least 1 IPTp treatment and have a recorded pregnancy outcome (abortion, still birth, or live birth) will be included into this analysis. This restriction applies to all analyses except for analyses of reported drug side effects (see 9. below).

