### Delivery and Assessment of IPTp intervention

The primary assessment of the IPTp intervention will take place at delivery.

The specific tasks to be completed by the field study team at the delivery visit are as follows:

Baby:

- Record pregnancy outcome (i.e. live birth, stillbirth, abortion)
- Record birth weight
- Collect a heel prick blood sample (200 µl)
  - Prepare thin and thick blood smears
  - Archive a portion of the blood sample for laboratory analyses
  - Measure Hb using Hemacue
- Collect a cord blood sample (approximately 10 ml)
  - Cord haemoglobin concentration
  - Archive a portion of the blood sample for laboratory analyses

Mother

- Interview and record
  - history of bednet use since previous visit
  - history of malaria treatment since previous visit
- Collect maternal peripheral blood (10 ml)
  - Prepare thin and thick blood smears
  - Measure Hb using Hemacue
  - Archive a portion of the blood sample for laboratory analyses
- Collect placental blood films and placental biopsies
- Collect a per-nasal swab

Check the health records booklet for recent health centre visits and record applicable information.

Mothers that deliver at home will be asked to visit Modilon Hospital or a participating health center within no more than a week. In these cases the following tasks will be performed:

Baby:

- Record day of birth
- Record pregnancy outcome (i.e. live birth, stillbirth, abortion)
- Record weight
- Collect a heel prick blood sample (200 µl)
  - Prepare thin and thick blood smears
  - Archive a portion of the blood sample for laboratory analyses
  - Measure Hb using Hemacue

Mother

- Interview and record
  - history of bednet use since previous visit
  - history of malaria treatment since previous visit
- Collect maternal peripheral blood (10 ml)
  - Prepare thin and thick blood smears
  - Measure Hb using Hemacue
  - Archive a portion of the blood sample for laboratory analyses

Check the health records booklet for recent health centre visits and record applicable information.

Before discharge, the field study team will schedule a 6 week post partum visit with the woman and her baby.

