The prevalence of carriage of S pneumoniae and of antibiotic resistance will be determined in nasopharyngeal swabs by routine culture and disc diffusion, respectively. Isolates will be stored for further characterization.

1. ***Maternal, perinatal and infant mortality rates.***

The following mortality rates will be determined:

1. Maternal mortality rate (enrolment to 6 weeks post partum). Determined by home visits to communities where mothers lived, and interview of family members and other relevant individuals.
2. Abortion/stillbirth rates. These are defined as death of a fetus before delivery. Abortion is a death before 22 weeks estimated gestation and stillbirth is a death at or after 22 weeks gestation
3. Perinatal mortality rates. These are defined as death (due to any cause) of a child from 22 weeks to 7 days post partum.
4. Infant mortality rate (0-12 months). All cause infant death will be recorded.
5. **Impact of IPTp on development of immunity to malaria in pregnancy**

A detailed description of immunological outcome measures will be given in a separate immunology sub-protocol.

1. **Characteristics of parasites infecting pregnant women.**

A detailed description of parasitological outcome measures will be given in a separate immunology sub-protocol.

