### Secondary Outcome Measures

1. **Prevalence of *P. falciparum* malaria at delivery by microscopy**

This outcome measure will be analysed in women in whom blood films (peripheral and/or placental) are collected at delivery.

1. **Prevalence of *P. falciparum* malaria at delivery by histology**

This outcome measure will be analysed in all women from whom an assessable placental biopsy is collected at delivery.

1. **Maternal Hb at delivery by histology**

This outcome measure will be analysed in all women from whom an Hb measurement at delivery is available.

1. **Incidence of symptomatic malaria**This outcome will be analysed in all women that have had 1 IPTp treatment
2. **Prevalence of STIs on Vaginal swab at 28-34 weeks gestation**

This outcome measure will be analysed in all women in whom an assessable swab is collected at 28-34 weeks. Rates of carriage of N gonorrhoeae, C trachomatis and T vaginalis (assessed by PCR) will be compared between groups.

1. **Maternal, perinatal and infant mortality rates**

All deaths, irrespective of cause of death, occurring in the cohort of pregnant women and their fetuses or children between Enrolment and Final Evaluation Visit (6 weeks post partum for pregnant women, deaths from 22 weeks gestation to 28 days post partum for perinatal mortality, deaths from day 28 of life to 12 months of age for infants) will be considered for this analysis

1. **Reported side effects / Adverse events**

All reported side effects following IPTp treatment, irrespective of total number of treatments a woman received, will be considered for these analyses.

1. **Molecular markers of SP resistance**

This endpoint will be assessed in a random sample of PCR-positive samples collected at 2nd treatment and at delivery.

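### The recorded-outcome and missed-treatment exclusions in 11.1.2 and 11.3, read literally, cover mortality and conflict with the rule that counts all deaths from enrolment; the plan does not say which prevails

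*Combined protocol and SAP*

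**What the plan says.** Four places in the combined protocol and SAP bear on who enters the mortality analysis.

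- Section 11.1.2, in the text on the LBW outcome: "Only women who receive at least 1 IPTp treatment and have a recorded pregnancy outcome (abortion, still birth, or live birth) will be included". The next sentence widens the scope: "This restriction applies to all analyses except for analyses of reported drug side effects".
- Section 11.3 removes women who missed more than two treatments from all analyses and again exempts only drug side effects.
- Section 11.1.3, mortality item, takes in "All deaths, irrespective of cause of death, occurring in the cohort of pregnant women and their fetuses or children between Enrolment and Final Evaluation Visit".
- Section 8.1.2 runs maternal mortality from enrolment to 6 weeks post partum and says how these deaths are found: "Determined by home visits to communities where mothers lived, and interview of family members and other relevant individuals".

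Pregnancy outcome is recorded at the delivery visit, or at a facility visit within a week of a home birth (section 6.1.5). No section says which rule governs mortality.

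**The concern.** Requiring a recorded end of pregnancy makes inclusion in a death endpoint depend on something that death can prevent. A woman who dies while still pregnant may never reach the contact at which the outcome is recorded. Excluding her takes a death out of the numerator and a woman at risk out of the denominator, on the basis of an event after randomisation. The comparison is then no longer between the groups as randomised.

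Safety is part of the primary objective in the synopsis, and mortality by group is secondary objective 12. Because two incompatible rules stand in the plan, an analyst could produce two different sets of mortality counts from the same data and defend either, possibly after seeing them.

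**Working it through.** **1. Scope of the exclusions.** Section 11.1.2 sets two conditions: (a) at least one course and (b) a recorded pregnancy outcome. It applies them to every analysis but one, and mortality is not the exception. Section 11.3 has the same structure. Sections 8.1.2 and 11.1.3 attach neither condition to deaths.

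**2. Women on whom the rules disagree.**

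| Situation | 8.1.2 / 11.1.3 | 11.1.2 |
| --- | --- | --- |
| Enrolled in first trimester, dies before first course (possible under 6.1.4) | counted | fails (a) |
| Treated, dies undelivered | counted | fails (b), unless coded as abortion or stillbirth |
| Treated, death found by tracing, no pregnancy outcome obtained | counted | fails (b) |
| Treated, death found by tracing, pregnancy outcome obtained | counted | counted |

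The 11.3 exclusion adds little here. Three courses are scheduled, so a woman who took the first can miss at most 3 − 1 = 2, which is not more than two. Taken literally it removes only women with no course, who already fail (a). It matters because it repeats the single exemption.

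**3. Fetal side.** Section 8.1.2 treats fetal death at or after 22 weeks as stillbirth and counts perinatal deaths from 22 weeks. An undelivered maternal death after that point therefore also involves a perinatal death, and excluding the mother can remove both.

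**4. Size.** The plan gives no mortality rate, and no sample size or power for mortality, so there is no figure to reproduce.

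- *Denominator, upper bound.* From section 11.2, 1396 women per arm and 20% loss: 0.20 × 1396 = 279 per arm, leaving 1396 − 279 = 1117. For the whole trial, 0.20 × 2792 = 558. This assumes that every lost woman lacks a recorded outcome.
- *Numerator, assumptions only.* Let r be maternal mortality per 100,000 and f the share of deaths with no recorded outcome. Neither is in the documents. Expected deaths in both arms together are 2792 × r / 100,000; deaths dropped are f times that.

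| Assumed r | Expected deaths | Dropped at f = 25% | Dropped at f = 50% |
| --- | --- | --- | --- |
| 100 | 2.8 | 0.7 | 1.4 |
| 300 | 8.4 | 2.1 | 4.2 |
| 700 | 19.5 | 4.9 | 9.8 |

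Across this range, about one to ten deaths would depend on which rule is applied, out of roughly 3 to 20.

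**The case against.** The strongest reply is that section 11.1.3 gives each secondary outcome its own population (films collected, assessable biopsy, haemoglobin available, and so on) and gives mortality the widest one. The restricting sentence sits under low birth weight. On that reading the specific rule governs and no death is lost. This is plausible, and a reader should not infer that the mortality analysis is settled as the restricted one. But 11.1.2 speaks of all analyses, names a single exception, and is echoed in 11.3. The plan supports either reading.

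Three further points stand in part.

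- Section 8.1.2 defines abortion and stillbirth as fetal death before delivery, so a woman who dies undelivered could be given one of those outcomes. The plan never says that she will be.
- Family interviews may supply a pregnancy outcome, and village reporters look for deliveries outside facilities (section 6.1.1). A reader might infer that every home-traced death is discarded. Only those for which tracing yields no outcome would be.
- A reader might also infer that deaths disappear from the safety data. The documents do not support this. Section 9.3.1 puts every death on a serious adverse event form, and section 9.3 sends such events to the DSMB and the Safety Working Group. The exempt item in 11.1.3 is headed as covering adverse events as well as side effects, so deaths probably fall within it.

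It is also fair to say that mortality is an outcome to be documented by group, with no test or model in section 11.4. That limits the consequence to the reported rates, but does not say what those rates should be.

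**Conclusion.** The conflict is real and rests on the text alone. Sections 11.1.2 and 11.3, taken literally, reach the mortality outcome; sections 8.1.2 and 11.1.3 count all deaths from enrolment; nothing sets the order of precedence. If 11.1.2 is followed as written, the mortality rates lose women for a reason that death itself can cause.

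The documents do not give the size. The fall to 1117 per arm is an upper bound, because some lost women will have an outcome traced and others will have unknown vital status under any rule. The death counts above are illustrations on assumed rates. They show only that, with so few events, the choice of rule could alter the comparison between arms; no particular distortion or direction can be claimed. The effect is confined to the maternal, perinatal and infant mortality rates. Expedited safety reporting is untouched, and the adverse-event analysis probably is too.

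**What to change.** - In 11.1.2 and 11.3, exempt the mortality outcome from the recorded-outcome and missed-treatment exclusions.
- In 11.1.3, analyse mortality in all randomised women by allocated arm, whether or not a pregnancy outcome is recorded, followed to death, last contact or the end of the stated window.
- List deaths between enrolment and randomisation or first treatment separately. The envelope is opened immediately before treatment (section 6.3.3), so these are mainly women enrolled in the first trimester. Without this line they would vanish from an outcome that the plan starts at enrolment.
- State how a maternal death while undelivered is counted for fetal and perinatal mortality.
- Settle the windows at the same time: perinatal deaths run to 7 days in 8.1.2 but to 28 days in 11.1.3, and infant deaths start at birth in the first and at day 28 in the second.

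The cost is a few sentences. The deaths are already to be collected under 8.1.2 and 9.3.1, and the sample size does not change.
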